### 9.3 Treatment Evaluation

#### 9.3.1. Treatment evaluation during TNT

Patients in Arm 1 will undergo a digital rectal exam and proctoscopic exam within 4 weeks (+/- 14 days) after the last day of chemotherapy of the last cycle (disconnect date of FOLFOX cycle 8 or the last day of capecitabine of CapeOX cycle 5). Patients in Arm 2 will undergo digital rectal exam and proctoscopic exam within 4 weeks (+/- 14 days) after the last day of radiation. If the tumor cannot be reached on digital rectal exam, this should be noted on the checklist and evaluation. Thus, the below criteria for digital rectal exam should only be applied for palpable tumors.

The primary tumor and the regional lymph nodes will be evaluated by digital rectal exam, and evaluated and measured by endoscopic exam. MSKCC patients will also undergo an MRI exam. MRI at the interval evaluation is optional for sites.

The following criteria should be used to best describe response during neoadjuvant treatment. The characteristic(s) which define the lowest level of response (furthest to the left on the schema below) will be used to define response. Checklists will be provided and the data will be entered into a central database.

|                            | Progressive Disease                                                 | Stable Disease or Partial Response                                                                                                                                                                                          | Near Complete Response                                                                                                                                                                                        | Complete Response                                                                                                                                                                                             |

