|----------------------------|----------------------------------------------------------------------------|------------------------------------------------------------------------------------------------------------------------------------------------------------------------------------------------------------------------------------|----------------------------------------------------------------------------------------------------------------------------------------------------------------------------------------------------------------------|----------------------------------------------------------------------------------------------------------------------------------------------------------------------------------------------------------------------|
| Endoscopic Exam     | 
 
• Increase in tumor size
 
 | 
 
• Partial response
 
• No change in size
 
                                                                                                                                  | 
 
• Irregular mucosa
 
• Small mucosal nodules or minor mucosal abnormality
 
• Superficial ulceration
 
• Mild persisting erythema of the scar
 
 | 
 
• Flat, white scar
 
• Telangiectasia
 
• No ulcer
 
• No nodularity
 
                                                                          |
| Digital Rectal Exam | 
 
• Palpable tumor nodules
 
 | 
 
• Palpable tumor nodules
 
                                                                                                                                                         | 
 
• Smooth induration or minor mucosal abnormalities
 
                                                                                                                 | 
 
• Normal
 
                                                                                                                                                           |

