| MRI-DW | 
 
•
 
 | 
 
• Stable or continued diminution in signal (no new focal signal)
 
 | 
 
• Significant regression of signal on B800-B1000
 
 | 
 
• No visible signal on B800-B1000
AND/OR
 
• Uniform, linear signal in wall above tumor is acceptable
 
 |

Patients who present with stable disease, partial response, near-complete or complete clinical response should continue TNT. Patients who present with tumor progression should be treated according to standard practice per institutional guidelines. The total time between treatment arms can be up to but not more than 8 weeks.

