### 9.3.2. Treatment evaluation at completion of TNT

Patients in both groups are required to undergo tumor assessment and re-staging by endoscopic exam, digital rectal exam, rectal MRI, and evaluation of potential metastatic disease by CT of the chest, abdominal, and pelvis, within 8 weeks (+/- 4 weeks) after completion of TNT (last day of radiation for Arm 1, and disconnect date for FOLFOX or last capecitabine for CapeOX in Arm 2).

The following criteria should be used to determine tumor response to TNT at the end of treatment. The characteristic(s) which define the lowest level of response (furthest to the right on the schema below) will be used to define response. Checklists will be provided and the data will be entered into a central database.

|                            | Complete Response                                                                                                                                                                                                                             | Near Complete Response                                                                                                                                                           | Incomplete Response                                                                                                                               |
|----------------------------|------------------------------------------------------------------------------------------------------------------------------------------------------------------------------------------------------------------------------------------------------|-----------------------------------------------------------------------------------------------------------------------------------------------------------------------------------------|----------------------------------------------------------------------------------------------------------------------------------------------------------|

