|---------------|--------------------------------------------------------------------------------------------------------------------------------------------------------------------------------------------------------------------------------------------|----------------------------------------------------------------------------------------------------|------------------------------------------------------------------------------------------------------|
| MRI-DW | 
 
• No visible signal on B800-B1000
 
 
AND/OR
 
 
• Uniform, linear signal in wall above tumor is acceptable
 
 | 
 
• Significant regression of signal on B800-B1000
 
 | 
 
• Insignificant regression of signal on B800-B1000
 
 |
|---------------|--------------------------------------------------------------------------------------------------------------------------------------------------------------------------------------------------------------------------------------------|----------------------------------------------------------------------------------------------------|------------------------------------------------------------------------------------------------------|

\*Incomplete response indicates that tumor has not shrunk sufficiently to implement non-operative management safely. This category applies to tumors which do not meet the Complete Response or Near Complete Response criteria.

In general, clinical examination will prevail over imaging assessment of primary tumor response.

Patients with complete or near complete clinical response at the time of re-staging after TNT will be entered into the NOM protocol. Patients with incomplete response will proceed to TME. Incomplete response is defined as having neither a near complete response nor complete response.

The MSKCC PI and radiologist are available to assist with resolving local discrepancies.

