Discrepancies between clinical examination and imaging will be resolved by the local investigator. In the event that the MSKCC radiologist disagrees with a participating site interval or re-staging assessment and feels that it may place the patient at undue risk at the interval or restaging, these discrepancies will be communicated back to the participating site PI and radiologist. No response will be communicated back to the participating site if, upon review of submitted images, there are no discrepancies in assessment.

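### Response classification in 9.3.1, 9.3.2 and 9.5 conflicts with itself: palpable nodules in a stable or responding tumor read as progression at the interval evaluation, and unranked rules at re-staging give both TME and NOM when a good clinical examination meets an incomplete MRI

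*Protocol*

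**What the plan says.** **Interval evaluation (Protocol 9.3.1).** Four ordered columns run from Progressive Disease on the left to Complete Response on the right. The tie-break is: "The characteristic(s) which define the lowest level of response (furthest to the left on the schema below) will be used to define response".

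- Endoscopic criterion for Progressive Disease: "Increase in tumor size". Partial response and unchanged size sit in the next column.
- Digital rectal exam (DRE) criterion: "Palpable tumor nodules", printed identically under Progressive Disease and under Stable Disease/Partial Response. Smooth induration is near complete.
- Scope of the DRE row: "the below criteria for digital rectal exam should only be applied for palpable tumors", that is, tumors within reach of the finger.
- Consequence: "Patients who present with tumor progression should be treated according to standard practice per institutional guidelines". Every other category continues neoadjuvant therapy, an intent repeated in 1.0, 4.1 and 4.2.

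**Re-staging (Protocol 9.3.2 and 9.5).** The table has rows for endoscopy, DRE, T2-weighted MRI and diffusion-weighted MRI. Its rule is: "The characteristic(s) which define the lowest level of response (furthest to the right on the schema below) will be used to define response". Below the table comes: "In general, clinical examination will prevail over imaging assessment of primary tumor response". Section 9.5 adds: "Discrepancies between clinical examination and imaging will be resolved by the local investigator". Complete and near complete response lead to NOM; incomplete response leads to TME.

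**The concern.** These rules decide two things: who stays on total neoadjuvant therapy after the interval evaluation, and who enters NOM rather than TME. A rule that misclassifies when followed, or that can be followed in two ways, leaves each site to choose its own reading in an unblinded trial.

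NOM/TME membership feeds:

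- organ preservation, which 14.1 and 14.2 give as the reason for raising accrual to 325;
- the pick-the-winner rule in 14.2, which counts NOM patients alive and disease-free at 3 years and turns on a difference of 5;
- the NOM and TME groups in the quality-of-life comparison (14.3);
- the population monitored by the R1-resection stopping rule (14.5), namely NOM patients who later need TME;
- the primary endpoint, because 12.0 does not count regrowth under NOM as recurrence if TME then achieves negative margins, but does count local recurrence after any TME.

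The preliminary proportions selected for NOM in 14.2 (66% and 79%) are themselves products of this classification.

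**Working it through.** The plan states no figure to reproduce. The check applies the written rules to every possible combination of findings. The counts below are combinations, not patients, and no combination is assumed more likely than another.

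**Interval evaluation.** Inputs are 4 endoscopic levels and 3 DRE findings (nodules, smooth induration, normal), so 4 × 3 = 12 combinations. Rule: take the leftmost column reached by either row. MRI is left out because 9.3.1 makes it optional outside the coordinating center, where 7.0 expects 238 of 325 patients (73%). An added row could only move a case further left.

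| Endoscopy | DRE | As written | If nodules counted only as stable/partial |
|---|---|---|---|
| Growth | Nodules | Progression | Progression |
| Partial response or no change | Nodules | Progression | Stable/partial |
| Near complete | Nodules | Progression | Stable/partial |
| Complete | Nodules | Progression | Stable/partial |

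All 4 combinations with nodules become progression, yet only 1 of the 4 shows endoscopic growth. The other 3 are progression through the DRE row alone. The nodule entry in the stable/partial column can never decide a case. The remaining 8 combinations come out the same under both readings. The second row of the table is the plain contradiction: both of its findings are listed under Stable Disease/Partial Response, yet the patient is classed as progression.

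**Re-staging.** Inputs are 3 levels (complete, near complete, incomplete) for each of endoscopy, DRE, T2-weighted and diffusion-weighted MRI, so 3⁴ = 81 combinations. NOM requires that no deciding row is incomplete.

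- Rule A (worst of all four rows): NOM in 2⁴ = 16.
- Rule B (worst of the two clinical rows; MRI yields): NOM in 2² × 3² = 36.
- Disagreement: both clinical rows better than incomplete (2² = 4) and at least one MRI row incomplete (3² − 2² = 5), so 4 × 5 = 20. All 20 are TME under A and NOM under B; the reverse never occurs.
- With T2-weighted MRI only (3³ = 27): NOM in 2³ = 8 under A and 2² × 3 = 12 under B, with 4 in disagreement.

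Example: endoscopy and DRE near complete, with insignificant regression on diffusion-weighted MRI. Rule A gives incomplete response and TME; rule B gives near complete response and NOM. Section 9.5 gives whichever the local investigator decides.

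**The case against.** **On the interval table.** A descriptor shared by two columns arguably defines neither, so endoscopy should separate progression from stable disease. That fits the repeated intent that only tumor progression leaves the pathway, and it is probably what the drafters meant. But the written rule takes the leftmost column a finding reaches, so the sensible reading requires setting that rule aside.

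**On re-staging.** The worst-finding rule could be a default, the clinical-examination sentence a more specific override, and 9.5 the statement of who decides. The override is qualified: it holds in general, and for the primary tumor. The coordinating center's investigator and radiologist are available to help, and the central radiologist reports disagreements that may put a patient at undue risk. All this is in the text and softens the conflict. It does not supply a ranking: nothing says when the exception applies or whether it reaches nodal findings, and central feedback is limited to selected cases (9.5, 12.0).

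**Stronger readings that the documents do not support.**

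- A reader might infer that any palpable tumor is progression. The entry concerns palpable nodules; smooth induration is near complete, and the row applies only to reachable tumors.
- A reader might infer that every disagreement between examination and MRI is affected. Only a complete or near complete examination with an incomplete MRI changes the assignment.
- A reader might assume a discordance rate and set the resulting patients per arm against the winning margin of 5. The protocol gives no such rate. The margin is a between-arm difference in disease-free NOM patients at 3 years, used only if both arms meet the DFS endpoint. Misassignment acting alike in both arms would largely cancel.
- A reader might infer a demonstrated bias between arms. Randomization is stratified by institution (15.2), which balances site habits across arms. It does not remove effects that differ by arm, and the arms reach the interval evaluation after different treatments.
- A reader might infer that misclassified patients drop out of the DFS analysis. Section 13.0 keeps them in follow-up on an intent-to-treat basis.

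**Conclusion.** The point holds as two defects in the current text. At the interval evaluation, following the written rule classes palpable nodules with stable or partly regressed disease as progression, against the protocol's own intent. At re-staging, three unranked rules leave the assignment undetermined when examination is complete or near complete and MRI is incomplete.

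The size in patients cannot be derived from the documents. What can be shown is the extent within the rules: 3 of the 4 interval combinations with nodules are progression through the DRE row alone, and 20 of 81 re-staging combinations (4 of 27 without diffusion weighting) are assigned differently by rules A and B. This rests on reading the leftmost and rightmost rules literally and on taking rule B as letting the clinical rows decide.

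The main consequence is that NOM/TME membership lacks one reproducible definition across sites, which carries into every analysis that uses it. Bias in the between-arm comparison is possible but not shown.

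**What to change.** The clinical team must reconcile the passages; which rule is right is a clinical decision.

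1. In 9.3.1, make the DRE descriptors for Progressive Disease and Stable Disease/Partial Response mutually exclusive.
2. In 9.3.2, state one precedence rule, including when any exception applies and whether it covers nodal findings, and remove or subordinate the conflicting sentence.
3. Align 9.5 and the interval and re-staging checklists with that rule.
4. Once the rule is stated, report by arm how many patients were assigned to NOM or TME differently from it. This cannot be done before the rule is fixed.

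The cost is an amendment to a few sentences and one table row, plus a checklist update. Step 4 needs no new data collection, provided the central database holds the findings row by row; 9.3.1 and 9.3.2 say checklist data are entered there. Since 14.1 reports the original accrual as complete, the amendment can govern only evaluations still to come, and step 4 describes those already made.

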### 9.3.2. Treatment evaluation at completion of TNT

Patients in both groups are required to undergo tumor assessment and re-staging by endoscopic exam, digital rectal exam, rectal MRI, and evaluation of potential metastatic disease by CT of the chest, abdominal, and pelvis, within 8 weeks (+/- 4 weeks) after completion of TNT (last day of radiation for Arm 1, and disconnect date for FOLFOX or last capecitabine for CapeOX in Arm 2).

The following criteria should be used to determine tumor response to TNT at the end of treatment. The characteristic(s) which define the lowest level of response (furthest to the right on the schema below) will be used to define response. Checklists will be provided and the data will be entered into a central database.

|                            | Complete Response                                                                                                                                                                                                                             | Near Complete Response                                                                                                                                                           | Incomplete Response                                                                                                                               |
|----------------------------|------------------------------------------------------------------------------------------------------------------------------------------------------------------------------------------------------------------------------------------------------|-----------------------------------------------------------------------------------------------------------------------------------------------------------------------------------------|----------------------------------------------------------------------------------------------------------------------------------------------------------|
| Endoscopic Exam     | 
 
• Flat whitish scar
 
• Telangiectasia
 
• No ulcer
 
• No nodularity
 
                                                                                                         | 
 
• Irregular mucosa
 
• Small mucosal nodules
 
• Superficial ulceration
 
• Mild persisting erythema of the scar
 
 | 
 
• Visible tumor
 
                                                                                        |
| Digital Rectal Exam | 
 
• Normal
 
                                                                                                                                                                                           | 
 
• Smooth induration or minor mucosal abnormalities
 
                                                                                    | 
 
• Palpable tumor nodules
 
                                                                               |
| MRI-T2W             | 
 
• Normal appearing bowel wall without any fibrosis in the tumor bed
 
• Only dark T2 signal, no intermediate T2 signal
 
• No visible lymph nodes or very few, small (<5mm nodes)
 
 | 
 
• Mostly dark T2 signal, some remaining intermediate signal
AND/OR
 
• Partial regression of lymph nodes
 
                   | 
 
• More intermediate than dark T2 signal, no T2 scar
AND/OR
 
• No regression of lymph nodes
 
 |

|               |                                                                                                                                                                                                                                            |                                                                                                    |                                                                                                      |
|---------------|--------------------------------------------------------------------------------------------------------------------------------------------------------------------------------------------------------------------------------------------|----------------------------------------------------------------------------------------------------|------------------------------------------------------------------------------------------------------|
| MRI-DW | 
 
• No visible signal on B800-B1000
 
 
AND/OR
 
 
• Uniform, linear signal in wall above tumor is acceptable
 
 | 
 
• Significant regression of signal on B800-B1000
 
 | 
 
• Insignificant regression of signal on B800-B1000
 
 |
|---------------|--------------------------------------------------------------------------------------------------------------------------------------------------------------------------------------------------------------------------------------------|----------------------------------------------------------------------------------------------------|------------------------------------------------------------------------------------------------------|

\*Incomplete response indicates that tumor has not shrunk sufficiently to implement non-operative management safely. This category applies to tumors which do not meet the Complete Response or Near Complete Response criteria.

In general, clinical examination will prevail over imaging assessment of primary tumor response.

Patients with complete or near complete clinical response at the time of re-staging after TNT will be entered into the NOM protocol. Patients with incomplete response will proceed to TME. Incomplete response is defined as having neither a near complete response nor complete response.

The MSKCC PI and radiologist are available to assist with resolving local discrepancies.

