#### **9.3.4.2 MRI/CT**

Standard and DW-MRI sequences will be obtained in 1.5T or 3T units by using a phased-array body coil. All imaging studies will be interpreted by expert radiology staff at the patient primary treatment center for patient eligibility, clinical staging, and tumor response, according to standard clinical criteria. Central radiology review will be performed to ensure consistency with tumor staging and assessment of response. Images will be submitted on discs to the coordinating center (MSKCC). Baseline images should be submitted within 5 business days of the consent with report. Images for the first two patients at each site will be reviewed by central radiology review at MSKCC for quality control purposes. For interval evaluation and restaging evaluation exams, images should be submitted within 10 business days of the exams with reports. Submitted reports should indicate N staging. N staging of N- or N+ are accepted. Discs will be submitted de-identified and in the DICOM format. All patient identifiers must be removed and the unique case number included. Disks should be mailed to the MSKCC Study Coordinator at the following address.

Attn: MSKCC Study Coordinator  
Memorial Sloan Kettering Cancer Center  
Department of Surgery, Colorectal Service  
[name]  
[name]

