## **12.0 CRITERIA FOR THERAPEUTIC RESPONSE/OUTCOME ASSESSMENT**

The primary objective of this study, 3-year DFS, will be assessed on the basis of surveillance procto/sigmoidoscopy, physical examination, and follow-up radiologic scans. For patients who receive TME or NOM, follow-up scans will occur according to current NCCN guidelines for rectal cancer surveillance. Patients in the NOM group will be evaluated using rectal MRI and endoscopic exam (section 10). Patients in the NOM group who undergo subsequent TME will be followed according to current NCCN guidelines. 3-year DFS will be defined as the percentage of patients alive without recurrence of disease at 3 years measured from the date of randomization. Patients in the NOM protocol who develop relapse at the site of the primary tumor but undergo curative TME with negative resection margins will not be counted as having recurrence. However, any patients developing local recurrence after TME, performed either immediately after neoadjuvant therapy or after a period of NOM, will be counted as having recurrence. Scans will be reviewed at MSKCC to resolve any discrepancies in interpretation. Scans showing equivocal evidence of local recurrence will be evaluated with additional imaging as necessary. Biopsy confirmation of local recurrence will be indicated for the purposes of the protocol. Isolated elevation of CEA, in the absence of other evidence of recurrent disease, will not be considered indicative of either local or systemic relapse. Symptomatic evidence of local recurrence will be corroborated on the basis of imaging and/or physical examination. Distant recurrence will also be assessed using follow-up CT scans of the chest, abdomen and pelvis. The MSKCC radiologist will review scans to resolve any discrepancies in interpretation. Central radiology review at MSKCC will review all incoming images and reports, but will only submit feedback on cases in which scans must be repeated or, in the case of interval or re-staging evaluations, where progression is identified in disagreement with the site investigator's assessment. Scans with equivocal evidence of distant recurrence will be evaluated via additional imaging, as

necessary. Biopsy confirmation of distant recurrence will be indicated for the purposes of the protocol.

Adverse events associated with CT and RT-CT will be assessed using the standard criteria described in section 11.0.

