Based on previous data, we anticipate a 20% NOM in the INCT arm, and 35% in the CNCT arm, after 3 years. The proportion of patients initially entered in the NOM protocol will be higher, but some will later relapse and require TME. For this reason, we anticipate that the proportion of patients with NOM at 3 years will be close to the pCR rates observed in previous studies. We estimated that the 222 patients required for the primary aim would be sufficient to detect differences in organ preservation rates. Our preliminary results indicate that the proportions of patients selected for NOM based on tumor response after completion of neoadjuvant therapy are much greater than expected: 66% in one arm and 79% in the other. Although many of these patients may eventually experience tumor regrowth requiring total mesorectal excision, the proportions of patients with a preserved rectum 3 years after diagnosis are likely to be greater than the original estimates. Therefore, based on the new information, we plan to increase accrual to 325 patients. There is limited information regarding treatment compliance and adverse events in patients who have received more than 4 or 6 cycles of INCT or CTNT. Therefore, these secondary objectives are considered exploratory. If both arms meet the endpoint in primary objective, we plan to use NOM rate to determine the more promising regimen using a “pick the winner” strategy. We will calculate the number of patients treated with NOM who are alive and free of disease 3 years following the start of the study. We will require at least 20 NOM patients in each arm to employ the following strategy: If there is a difference of 5 NOM patients between arms, the arm with more NOM patients will be deemed the winner. With 101 patients in each arm, 20% NOM in patients treated with INCT and 30% in patients treated with CNCT, we will have an 83% probability of selecting CNCT, a 1% probability of selecting INCT, and a 16% probability of considering the study inconclusive.

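### Sections 9.5 and 12.0 give incompatible rules on when the central MRI reader tells a site that it disagrees with the site's interval or re-staging assessment

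*Protocol*

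**What the plan says.** Section 9.3.2 (re-staging after TNT) sorts patients into Complete, Near Complete or Incomplete response. The first two go to NOM and the third to TME. The grading rule is: "The characteristic(s) which define the lowest level of response (furthest to the right on the schema below) will be used to define response". Below the table comes the qualifier: "In general, clinical examination will prevail over imaging assessment of primary tumor response". The footnote to the table says what the lowest category means: "Incomplete response indicates that tumor has not shrunk sufficiently to implement non-operative management safely".

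Section 9.5 (MRI) names who decides when the two sources differ: "Discrepancies between clinical examination and imaging will be resolved by the local investigator". It then deals with the case in which the MSKCC radiologist does not share a participating site's view at either evaluation. If that reader also "feels that it may place the patient at undue risk at the interval or restaging, these discrepancies will be communicated back". The recipients are the site's PI and radiologist. The only silence that 9.5 provides for is when the central reader finds no discrepancy.

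Section 12.0 (outcome assessment) has central review look at every incoming image and report, but says that it "will only submit feedback on cases in which scans must be repeated or, in the case of interval or re-staging evaluations, where progression" has been seen against the site investigator's view.

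Section 9.3.4.2 states the purpose of the central read: "Central radiology review will be performed to ensure consistency with tumor staging and assessment of response".

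**The concern.** Both sections govern the same message, from the same central reader, at the same two evaluations. Section 9.5 makes it depend on disagreement plus undue risk. Section 12.0 makes it depend on progression or a scan that must be repeated, and the word *only* closes the list.

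The rules part at the step that matters most for the patient. At re-staging the treatment boundary lies between Near Complete (NOM) and Incomplete (TME). A tumor that has not grown but has not shrunk enough is on the TME side of that boundary without having progressed. If 12.0 is followed as written, a site could start NOM without being told that the central reader graded the MRI Incomplete and thought the patient at undue risk. Section 17.0 names relapse during NOM that TME cannot salvage as a risk to patients who were deemed curable at registration.

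**Working it through.** The protocol states no figure on this point, so the check sets the two rules side by side and applies each to the possible cases.

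**Step 1. Does 12.0 really cover re-staging?** Yes. Much of 12.0 concerns recurrence during follow-up, but the limiting clause names interval and re-staging evaluations. It cannot be set aside as a rule for surveillance scans.

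**Step 2. Can progression be read to include Incomplete?** No. The interval table in 9.3.1 has a Progressive Disease column. The re-staging table in 9.3.2 has three levels, none of which is progression (0 of 3). Incomplete is defined by insufficient shrinkage, not by growth.

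**Step 3. Apply both rules.**

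| Case | Section 9.5 | Section 12.0 | Agree? |
|---|---|---|---|
| Scan technically inadequate | Site told | Site told | Yes |
| Central reader sees progression, site does not, and undue risk is judged present | Site told | Site told | Yes |
| Central and site assessments match | No message | No message | Yes |
| Re-staging: central read Incomplete, no progression, adequate scan; site says Complete or Near Complete; reader sees undue risk | Site told | No message | **No** |
| As above, but reader does not see undue risk | No message required | No message | Yes |
| Site's own MRI read is also Incomplete, examination prevails, and the central reader counts no discrepancy | No message | No message | Yes |

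Only the fourth case conflicts, and it needs two conditions: the central reader disagrees with the site's assessment, and the reader judges that this may put the patient at undue risk. The second condition is not far-fetched, because 9.3.2 itself equates Incomplete with NOM not being safe.

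**Step 4. Why the conflict bites at re-staging.** At the interval evaluation only progression changes treatment; every other category continues TNT (9.3.1). A trigger confined to progression is adequate there. At re-staging the treatment decision turns on Incomplete, which that trigger does not reach.

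**Step 5. How many patients do the rules bear on?** Section 7.0 expects 87 patients at MSKCC and 238 at outside centers: 238/325 = 73.2%. Section 14.2 gives preliminary selection for NOM of "66% in one arm and 79% in the other". Assume that these rates hold at the outside centers and that the arms are equal there (238/2 = 119 each). Then 119 × 0.66 + 119 × 0.79 = 78.54 + 94.01 = 172.55, so about 173 outside patients would enter NOM on a site classification. This is the group in which the conflict can arise, not the number affected. The protocol gives no rate of central versus site disagreement, so the number affected cannot be computed.

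**The case against.** The strongest reply has four parts.

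*Section 9.5 would win in practice.* It is the specific section on MRI handling and gives a positive safety instruction, so a central reader would plausibly follow it. That may be so, but 12.0 uses an exclusive word and names the same evaluations. A reader who follows 12.0 is also following the protocol.

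*The message would often change nothing.* Examination generally prevails over imaging of the primary tumor and the local investigator decides, so many patients would stay on NOM. This stands as a limit on the size of the point. It does not justify withholding information that 9.5 says the decider should have.

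*Other safeguards exist.* Site responses are subject to the Therapeutic Response Review Committee (16.1.2). Examination notes are reviewed centrally for the first two patients per site and then case by case (9.3.4.1). NOM patients have endoscopy and MRI from 3–6 months (section 10), and progression leads to TME (9.3.3). Section 14.5 has a stopping rule for R1 resections, and 17.0 reports that relapses under close surveillance have been salvaged. The MSKCC PI and radiologist are also available to help (9.3.2). All of this stands and keeps the point modest. None of these provisions, however, sends the central MRI read to the site before NOM starts.

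*Section 9.3.2 is not in error.* A reader might infer that its lowest-level rule and its preference for examination contradict each other. They need not: the second reads as a qualifier limited to the primary tumor, with deliberate discretion and a decider named in 9.5. The absence of a fixed override criterion is a choice. Likewise, 9.3.4.2 states why central review is done, which fits 9.5 better than 12.0, but it sets no reporting rule and does not settle the conflict.

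**Conclusion.** The two sections contradict each other, and 12.0 is the one to correct. Followed literally, it withholds a safety message that 9.5 requires. This conclusion rests on the text alone and on no assumed rate.

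Its scope is narrow. It concerns participating-site patients whose central re-staging read is Incomplete without progression, whom the site has classed Complete or Near Complete, and for whom the central reader sees undue risk. A reader might infer that every mismatch between examination and MRI falls into this gap. It does not: where the site's own radiologist has already read Incomplete, the site knows, and neither rule need apply. The figure of about 173 outside NOM entrants is a ceiling on the group concerned, under the stated assumptions of equal arms and unchanged selection rates.

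Because NOM status feeds the organ-preservation comparison and the selection between arms in 14.2, a reader might also infer a bias there or in disease-free survival. The documents do not support that. They give no discordance rate overall or by arm, and both rules apply to both arms alike.

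**What to change.** In 12.0, replace the part of the clause that limits interval and re-staging feedback to progression with: *where the central reader disagrees with the site's assessment, including on progression, and the disagreement may place the patient at undue risk, as in section 9.5*. The trigger for scans that must be repeated stays as it is, and the local investigator keeps the decision.

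The cost is one clause and an occasional extra message to a site. No scan, visit or read is added, because 12.0 already has central review look at all incoming images.

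Two further changes are optional and not part of the error. One is to state within the lowest-level sentence of 9.3.2 that the preference for examination is an exception for the primary tumor. The other is to require that every discordant Incomplete read be reported; this would remove a judgement that 9.5 deliberately leaves to the central reader.
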